#### Qualitative interviews

Qualitative interviews are undertaken during the internal pilot to explore variables impacting recruitment, retention rates and discontinuation. The Topic Guide is included in Supplementary file 12. Interviews are administered by phone to staff in sites open for recruitment for at least 4 weeks, participants who withdraw/are withdrawn during the pre-randomisation phase or before week 12 in the randomisation phase, and randomised participants who remain in the trial until week 12. Interviews will conclude for each group once data saturation has been reached.

### Sample size, power and effect size

The estimated sample size for randomisation is based on the CEQUEL study [32] that included similar participants in a depressive episode of BD from the UK NHS, and who had weekly remote monitoring of mood over a 52 week period. Dropout rates in this study were 20% at 12 weeks and 50% at 52 weeks. A power calculation demonstrates that 290 participants provides a 90% power of detecting a 3-point difference in QIDS-SR [33] between pramipexole and placebo (*p* < 0.05), based on a two-sample t-test at 12 weeks with a QIDS-SR [33] standard deviation of 7 and assuming a 20% dropout rate as seen in the CEQUEL study [32]. This sample size also provides approximately 80% power of detecting a 3.3 point difference in QIDS-SR scores [33] between the treatment arms at week 48 assuming the 50% dropout rate seen in CEQUEL [32] and the standard deviation used above. In a study of a similar population, a drop-out rate of 30% was experienced during the pre-randomisation phase [46]. As a result, it is anticipated that PAX-BD will need to recruit approximately 414 participants into the pre-randomisation phase trial to achieve the target of 290 participants randomised.

## Methods

### Study design

The PAX-BD study is a multicentre parallel group, double-blind, randomised, placebo-controlled superiority trial of the addition of pramipexole to ongoing mood stabiliser (lithium, valproate, carbamazepine or lamotrigine) treatment in patients suffering from a moderate to severe episode of bipolar depression who are operationally defined as having TRBD on the basis of non-response, intolerance, contraindication, clinically felt to be inappropriate or declined by patient of at least two NICE recommended treatments for bipolar depression (lamotrigine, quetiapine, olanzapine with or without fluoxetine), or lurasidone which is included as a recommended treatment in British Association for Psychopharmacology guidelines [47].

The study was initially funded and approved on the basis that an exclusion criterion for randomisation was ongoing treatment with an antipsychotic. Those participants on antipsychotics recruited into stage 1, were required to have these withdrawn. Early feedback during the study pilot phase indicated that this requirement was significantly negatively impacting on recruitment. As a result, this issue was reviewed. Since the original submission of the study design to the funder, increasing evidence has emerged suggesting that pramipexole’s mechanism of action in depression is via activation of dopamine D3 receptors. Pharmacologically, pramipexole appears to preferentially bind to D3 versus D2 receptors in vivo [48]. D3 receptor knock out mice have been reported to exhibit depressive and anxious features [49]. In addition, a wealth of recent data using highly selective D3 antagonists in animal models has demonstrated that D3 receptors play a critical role in reward processes [50, 51]. Further, PET imaging data in humans suggests D3 receptor expression may be related to motivation for rewards [52]. Recent data also suggests a positive effect of pramipexole on dendritic arborization and soma size mediated via increased brain derived neurotrophic factor (BDNF: 55), and that pramipexole can prevent inflammation induced depression-like behaviours in mice [53], both plausible mechanism of action in depression. On this basis, the HTA panel and the Medicines and Healthcare products Regulatory Agency (MHRA) approved an alteration to the protocol to allow participants to be on an antipsychotic at randomisation if the dose was at or below the level described in Table 2. These doses were determined based on the individual drug’s absolute D3 receptor affinity and the relative affinity for D2 versus D3 receptors.

**Table 2 Tab2:** List of antipsychotics and maximum daily dose allowed for randomisation eligibility

Drug	Maximum daily dose
Aripiprazole	15 mg
Aripiprazole depot	400 mg every 4 weeks
Chlorpromazine	200 mg
Flupentixol depot	200 mg every 4 weeks
Haloperidol	2 mg
Haloperidol depot	100 mg every 4 weeks
Lurasidone	111 mg
Olanzapine	10 mg
Olanzapine depot	150 mg every 2 weeks
Paliperidone	3 mg
Paliperidone depot	75 mg every month
Quetiapine	300 mg
Risperidone	1 mg
Risperidone depot	25 mg every 2 weeks
Zuclopenthixol depot	500 mg every 4 weeks

The study has two phases: a pre-randomisation phase and a post-randomisation phase. The pre-randomisation phase is to allow participants to adjust antipsychotic medication to minimise any possible antagonism of the effect of pramipexole and commence mood stabilisers, if needed; these doses must be stable for a minimum of four weeks prior to randomisation. If no changes to medication are required, the pre-randomisation phase lasts for four weeks from consent to randomisation to allow familiarisation with the data collection tools and confirm persistent depressive symptoms. The primary outcome point is 12 weeks after randomisation, with follow up of participants to 48 weeks, plus 4–6 weeks to allow for continuing or tapering of trial medication.

PAX-BD includes an internal pilot study to examine feasibility and acceptability of the study design and inform any remedial action to the study design if required. Qualitative and quantitative data is collected from participants during the pre-randomisation phase and up to 12 weeks post randomisation, along with qualitative interviews of research staff regarding recruitment and management of participants in the study. The trial funder stop criteria are, relative to recruitment of the first participant into the pre-randomisation phase of the trial, ≤ 50 participants randomised to either arm at 12 months with a ≤ 70% retention of those randomised at the primary outcome time point of 12 weeks. At 12 months post-consent to pre-randomisation of the first participant, the Trial Management Group (TMG) will review the number of participants randomised and the percentage retention at 12 weeks. These numbers will be passed to the Data Monitoring Committee (DMC) and Trial Steering Committee (TSC), for verification as to whether they meet the trial stopping criteria or not. The TSC monitor study progress and conduct, and an independent DMC are the only body with access to un-blinded data prior to the final data lock at study conclusion. Recruitment and retention rates will be reviewed on an ongoing basis by the TMG throughout the trial.

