### Objectives and measures

A key design feature of the PAX-BD study is that outcome measures are mainly collected remotely, mostly using self-report tools implemented on-line using the True Colours platform [32]. Three scales, the Quick Inventory for Depressive Symptomatology – Self Report (QIDS-SR) [33], Altman Self-rating Scale of Mania (ASRM) [34] scale and Generalised Anxiety Disorder-7 (GAD-7) [35] scale are completed on-line by participants weekly from recruitment into the pre-randomisation phase through to the end of follow up. To facilitate comparison of PAX-BD with other studies, the clinician-rated version of the QIDS (QIDS-C) [33], the Montgomery-Asberg Depression Rating Scale (MADRS) [36] and the Young Mania Rating Scale (YMRS) [37] are completed by phone by the study Research Assistants (RAs) at two time points. The timings of the administration of assessments is shown in the Schedule of Events (Table 1).

**Table 1 Tab1:** Schedule of Events

	Screening	Pre-randomisation	Screening and Randomisation	0	Treatment weeks (Post-randomisation)																												Tapering (5, 6, 7)	
					1	2	3	4	5	6	7	8	9 to 11	12	13 to 15	16	17 to 19	20	21 to 23	24	25 to 27	28	29 to 31	32	33 to 35	36	37 to 39	40	41 to 43	44	45 to 47	48	49 to 51	52*
Informed consent (1,2)	✓		✓																															
Demographics	✓	✓																																
Eligibility assessment	✓		✓																															
Randomisation			✓																															
RA safety monitoring call (3, 8)		✓		✓	✓	✓	✓	✓	✓	✓	✓	✓	✓	✓		✓		✓		✓		✓		✓		✓		✓		✓		✓	✓	✓
CSO contact (4)						✓				✓				✓						✓						✓						✓		✓
QIDS-SR, GAD-7 and ASRM		✓		✓	✓	✓	✓	✓	✓	✓	✓	✓	✓	✓	✓	✓	✓	✓	✓	✓	✓	✓	✓	✓	✓	✓	✓	✓	✓	✓	✓	✓	✓	✓
SHAPS				✓						✓				✓																				
WSAS				✓						✓				✓						✓						✓						✓		
TSQM										✓				✓		✓		✓		✓		✓		✓		✓		✓		✓		✓		
QUIP-RS				✓						✓				✓		✓		✓		✓		✓		✓		✓		✓		✓		✓		✓
MADRS, QIDS-C and YMRS				✓										✓																				
IMP Dispensings			✓					✓						✓				✓				✓				✓				✓				
Qualitative Interviews		✓												✓																				
Participant Vouchers														✓												✓								✓
Unblinding (9)																																✓		

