#### Inclusion criteria for entry to the pre-randomisation phase

Currently under the care of secondary care mental health services at screening with a plan for the patient to remain in secondary care throughout the period of the trial.A decision made by the patient’s clinical team that a change in medication is indicated.A current diagnosis of Bipolar Disorder (type I or II), defined as in Diagnostic and Statistical Manual of Mental Disorders-5 (DSM-5) [54], which is supported by the use of the Mini-International Neuropsychiatric Interview (MINI) [55].Currently depressed, i.e. meeting DSM-5 criteria for a Major Depressive Episode assessed via MINI and with a current Quick Inventory of Depressive Symptomology – Self Report (QIDS-SR) > 10 [33, 54].Current episode of depression failed to have responded to adequate trials, or lack of tolerability or patient declined/clinically inappropriate, of two different NICE recommended medications (quetiapine, olanzapine with or without fluoxetine, lamotrigine) or lurasidone. Adequacy of treatment trial defined using a custom designed ‘Bipolar Demographics and Treatment Questionnaire’ (BDTQ).Aged 18 or over at the point of consent.Willing and able to provide written informed consent prior to any trial procedures taking place.In the opinion of the investigator, is able to follow the trial prescription instructions and is able to manage 8 weeks supply of trial medication without risk of overdose.The patient, if female and of child-bearing potential, must have a negative pregnancy test [urine beta-human chorionic gonadotropin (β-hCG)].Women of child-bearing potential are required to use a highly effective contraceptive method during the pre-randomisation and post-randomisation phase of the trial. Highly effective methods of contraception include:

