#### Inclusion for randomisation

All criteria as for the pre-randomisation plus:
Been in pre-randomisation for a minimum of 23 calendar days.Severity of depression still meeting the criteria of QIDS-SR > 10.A minimum of two telephone phone calls with a trial RA and two on-line weekly symptom ratings have been completed during the pre-randomisation phaseOn mood stabilising medication (lithium, valproate, carbamazepine, lamotrigine)If on an antipsychotic this must be one listed, and at a dose of no more than the maximum stated in Table 2.All regular psychotropic medication, including antipsychotics and mood stabilisers, at a stable dose for a minimum of four weeks. Additionally, if a participant is on lamotrigine, quetiapine, olanzapine or lurasidone then this must have been at the current dose or higher for a minimum of three months.

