### Statistical analysis

Full details of all statistical analyses will be specified in a pre-defined Statistical Analysis Plan. Initial descriptive analysis will present the profile of the participants and investigate differences in demographic and outcome measures between the two treatment arms at baseline. If significant differences are found, the variable may be added to the models testing the relevant study hypothesis. A two-sided significance level of *p* < 0.05 will be used throughout.

Analysis of the primary outcome measure of QIDS-SR [33] at week 12 will use Analysis of Covariance (ANCOVA) to examine the difference between the treatment arms with adjustment for baseline covariates including initial QIDS-SR score, other minimisation factors and anxiety (GAD-7) score [35]. Other baseline covariates will be examined for potential inclusion during the modelling process.

Weekly repeated measures scores for QIDS-SR [33] will be examined to ascertain participant compliance in completion. Should this be judged sufficient, a mixed effects linear regression model will be used to account for the repeated measures over time in comparing this outcome between the treatment groups. Other secondary outcome measures include: the proportion of participants in remission at 12 and 48 weeks (QIDS-SR score ≤ 5), the proportion of participants who have achieved a response at 12 and 48 weeks (QIDS-SR score reduction of ≥50% from baseline), proportion of time over 48 weeks that participants are free of depressive symptoms (QIDS-SR score ≤ 5), proportion of time over 48 weeks that participants are free of manic symptoms (ASRM score ≤ 5) and changes in psychosocial function determined by the WSAS (35;37;42).

Secondary outcomes, other than those collected specifically for the health economic analysis, will be analysed in a similar manner to the primary outcome as described above. The ASRM and GAD-7 scores will also be examined on a weekly basis as described for the QIDS-SR [33–35]. MADRS, YMRS, SHAPS and QIDS-C between 0 and 12 weeks will be examined in a manner analogous to the primary analysis of the primary outcome [33, 36–38]. Safety and tolerability assessments will include ANCOVA of TSQM and QUIP-RS scores [40, 41], co-varying for baseline score and GAD-7 anxiety scores [35] given the impact of anxiety on tolerability and reported side effects with medication.

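### Weekly QIDS-SR scores are collected throughout the run-in, but the primary ANCOVA adjusts for only one of them; adding the run-in mean as a second covariate is a cheap gain in precision

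*Protocol article*

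**What the plan says.** All places are in the protocol article.

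- **Objectives and measures:** QIDS-SR, ASRM and GAD-7 "are completed on-line by participants weekly from recruitment into the pre-randomisation phase through to the end of follow up". Table 1 also lists QIDS-SR at week 0.
- **Study design:** if medication does not need to change, the pre-randomisation phase lasts four weeks, "to allow familiarisation with the data collection tools and confirm persistent depressive symptoms". Where antipsychotics are adjusted or a mood stabiliser is started, doses must then be stable for at least four weeks.
- **Inclusion criteria for entry to the pre-randomisation phase:** participants must be "meeting DSM-5 criteria for a Major Depressive Episode assessed via MINI and with a current Quick Inventory of Depressive Symptomology" score above 10.
- **Inclusion for randomisation:** "Been in pre-randomisation for a minimum of 23 calendar days" and "Severity of depression still meeting the criteria of QIDS-SR > 10". At least two weekly online ratings must have been completed. That is a completion rule and sets no level of severity.
- **Statistical analysis:** the week-12 QIDS-SR is analysed by ANCOVA with "adjustment for baseline covariates including initial QIDS-SR score, other minimisation factors and anxiety (GAD-7) score". It adds: "Other baseline covariates will be examined for potential inclusion during the modelling process". Response is a fall of at least 50% from baseline.

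**The concern.** By randomisation the trial holds several QIDS-SR ratings on most participants, made on the same scale as the primary outcome and close in time to baseline. The analysis section names one of them. A single weekly self-rating mixes the participant's usual level with that week's fluctuation, and the fluctuation weakens it as a predictor of week 12. If several ratings predict week 12 better than one, the treatment difference is estimated less precisely than the collected data allow.

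The word *initial* also leaves open whether the covariate is the score at run-in entry or at week 0, which lie at least 23 days apart. The reference to other minimisation factors, one of which is severity at randomisation, points towards the later score, but the text does not settle it.

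What is at stake is the width of the confidence interval, not its validity.

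**Working it through.** **1. The plan's own figure.** Inputs from the sample size section: difference 3, SD 7, two-sided 0.05, power 90%, dropout 20%.

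- Normal formula: n per arm = 2 × (1.960 + 1.282)² × 7² / 3² = 114.4, so 115. Then 230 / 0.8 = 287.5, so 288.
- Exact t-test: 116 per arm, and 232 / 0.8 = 290. Power at 116 per arm is 0.902 (0.904 by the normal formula).

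The stated 290 is reproduced. It uses no baseline adjustment, so nothing below changes it.

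**2. Gain from the run-in scores.** Let r be the correlation of one pre-randomisation score with week 12, R the correlation between weekly pre-randomisation scores, and k the number of scores used (week 0 plus k − 1 others). The documents give neither r nor R, so both are assumed, and both refer to the randomised sample. If every pair of weekly scores has the same correlation R, the best combination of the week-0 score and the mean of the others is their overall mean, so

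residual variance / SD² = 1 − r² × k / (1 + (k − 1)R).

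Middle case, r = 0.5 and R = 0.7:

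- k = 1: 1 − 0.25 = 0.750
- k = 2: 1 − 0.25 × 2/1.7 = 0.706, a cut of 6%
- k = 4: 1 − 0.25 × 4/3.1 = 0.677, a cut of 10%

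Reduction in residual variance against one score:

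| R | r | k = 2 | k = 4 |
|---|---|---|---|
| 0.5 | 0.4 | 6% | 11% |
| 0.5 | 0.5 | 11% | 20% |
| 0.6 | 0.4 | 5% | 8% |
| 0.6 | 0.5 | 8% | 14% |
| 0.6 | 0.6 | 14% | 24% |
| 0.7 | 0.4 | 3% | 6% |
| 0.7 | 0.5 | 6% | 10% |
| 0.7 | 0.6 | 10% | 16% |
| 0.8 | 0.4 | 2% | 3% |
| 0.8 | 0.5 | 4% | 6% |
| 0.8 | 0.6 | 6% | 10% |

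The pair R = 0.5, r = 0.6 is left out (it would give 19% and 34%), because a score some 12 weeks away would then correlate more strongly than one a week away.

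In the middle case, power for 3 points at 116 per arm (normal formula) goes from 0.965 with one baseline score to 0.973 with two and 0.978 with four.

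**3. Add the mean, or replace the score by the mean?** The gain in step 2 assumes independent week-to-week noise around a stable level. Suppose instead a pure autoregressive pattern with a lag-one correlation of 0.8 and r = 0.5 for the week-0 score.

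- Replacing week 0 by the mean of the last two scores gives r² = (0.5 × 1.8/2)² / (1.8/2) = 0.2025/0.9 = 0.225. The residual is 0.775 against 0.750, which is 3% worse.
- Keeping week 0 and adding the earlier scores leaves the residual at 0.750, because under this pattern they carry nothing beyond week 0.

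Adding the mean is therefore safe under both patterns, and replacing is not. The extra covariate costs one degree of freedom of roughly 230, about 1/230 = 0.4%.

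**4. Check on eligibility.** A simulation assumed a screened mean of 13 to 15, SD 4 to 5 and R of 0.6 to 0.9. The share of randomised participants whose underlying level is at or below the cut-off was about 2 to 10% if only one score had to exceed 10, about 1 to 4% under the protocol's two checks, and about 0.5 to 3% if the run-in mean had to exceed 10 as well.

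**The case against.** The strongest objection is that the derivation of the baseline covariate belongs in the SAP, which the article says will hold the full details and which is not shown; a lack of stated use may be only silence. That stands for the exact definition of the initial score, and its absence is not counted as a fault here. It does not dispose of the point. The article states a method, one score, and a better one is available from data already collected. The clause that lets other covariates be examined leaves room for the run-in mean, but as a choice made during modelling, and a covariate of the primary analysis is better fixed beforehand.

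A second objection is that the gain is small. That stands too: planned power does not depend on it, and any baseline adjustment already improves on the t-test.

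A reader might also infer something stronger: that entry rests on one high score, so that the trial randomises people who were only briefly depressed, and that regression to the mean distorts the result. The documents do not support this. The threshold applies at run-in entry, together with a MINI-supported episode, and again at least 23 days later. The intermediate scores carry no threshold, so someone low in between could still qualify, but step 4 suggests few would, and a further requirement would gain only about 0.3 to 1.4 percentage points. Regression to the mean acts on both randomised arms alike. It can raise within-arm change and response rates, but it does not bias the treatment contrast.

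**Conclusion.** The point holds as a matter of efficiency. The pre-randomisation QIDS-SR scores other than the single named covariate have no stated use in the analysis. Using them would lower ANCOVA residual variance by roughly 2 to 20% over most of the assumed range, by 24% in one corner of it, and by about 5 to 10% in middle cases. All of these figures rest on assumed correlations and on week-to-week noise around a stable level; under a pure autoregressive pattern the gain is nil. The treatment comparison is valid as planned, and the 290 and 90% are correct for the t-test they describe. This is a worthwhile refinement and not a defect that threatens the trial.

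**What to change.** In the Statistical analysis section, and in the SAP before unblinding:

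1. Define baseline QIDS-SR as the week-0 score taken before the first dose.
2. Pre-specify a second covariate for the primary ANCOVA: the mean of all weekly QIDS-SR ratings completed in the last four stable-dose weeks before randomisation, entered beside the week-0 score and not in its place.
3. State what is used if no rating falls in that window, for example the most recent earlier run-in rating. The two ratings required for randomisation could fall earlier when the run-in is long.

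Leave the eligibility threshold and the 50% response definition unchanged.

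The cost is analysis wording and one degree of freedom, with no new assessment and no effect on recruitment. The drawback is that participants contribute different numbers of ratings, so the mean is less precise for some. This weakens the gain somewhat but does not bias the comparison, because all these ratings precede randomisation.

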### Participants

#### Recruitment

Patients with TRBD are screened and recruited from secondary care services using clinician caseloads, databases and/or research registers in up to 40 mental health trusts across the UK. A list of study sites can be obtained at https://paxbd.org/about/recruiting-sites. Invitation letters and summary leaflets (Supplementary files 1 and 2) are available to advertise to patients directly by post, or channels such as secondary care clinics, websites, social media platforms and patient support groups.

Patients identified by clinicians and/or those showing interest are provided an initial information sheet (Supplementary file 3) in person or via post. Should they wish to proceed, Principal Investigators (PIs) or delegated clinicians take written informed consent (Supplementary file 4) and begin the screening process. Prior to randomisation participants receive a second information sheet (Supplementary file 5) and again are required to provide written informed consent (Supplementary file 6).

Participants who withdraw from the trial are given a withdrawal form (Supplementary file 7) and corresponding end of study information sheet (Supplementary file 8). Withdrawn participants are not replaced. Where a participant no longer wishes to take trial medication and gives consent for continued participation in the trial, they are followed up to 48 weeks. Participants who complete the trial to 48 weeks with trial medication are given the corresponding end of study information sheet (Supplementary file 9). See Fig. 1 for the participant pathway.

